## Abstract

**Background:**

Although obesity causes many adverse health consequences, modest weight loss reduces the incidence. There are effective interventions that help people to lose weight but weight regain is common and long term maintenance remains a critical challenge. As a high proportion of the population of most high and middle income countries are overweight, there are many people who would benefit from weight loss and its maintenance. Therefore, we need to find effective low cost scalable interventions to help people achieve this. One such intervention that has shown promise is regular self-weighing, to check progress against a target, however there is no trial that has tested this using a randomised controlled design (RCT). The aim of this RCT is to evaluate the effectiveness and cost effectiveness of a brief behavioural intervention delivered by non-specialist staff to promote regular self-weighing to prevent weight regain after intentional weight loss.

**Methods:**

A randomised trial of 560 adults who have lost ≥5 % of their initial body weight through a 12 week weight loss programme. The comparator group receive a weight maintenance leaflet, a diagram representing healthy diet composition, and a list of websites for weight control. The intervention group receive the same plus minimally trained telephonists will ask participants to set a weight target and encourage them to weigh themselves daily, and provide support materials such as a weight record card. The primary outcome is the difference between groups in weight change from baseline to 12 months.

**Discussion:**

If effective, this study will provide public health agencies with a simple, low cost maintenance intervention that could be implemented immediately.

**Trial registration:**

ISRCTN52341938 Date Registered: 31/03/2014

## Background

The global prevalence of obesity is estimated to be approximately 24 % [1] and is a significant cause of morbidity in terms of increased risk of type 2 diabetes, cardiovascular disease and many cancers [2–4]. Although many behavioural weight loss treatments are effective in the short term, long term maintenance remains a critical challenge. The period after initial weight loss is when people are at highest risk of weight regain [5]. Few people (1 in 10) recover from even minor lapses of 1–2 kg of regain in weight [5]. Therefore preventing small regains from turning into larger relapses appears critical to achieving effective long term weight control.

### Weight loss maintenance

Compared with weight loss trials, relatively few studies have focused on weight maintenance and those trials that do exist have tended to evaluate intensive interventions. A recent review of RCTs of weight loss maintenance interventions that enrolled obese adults following clinically significant weight loss identified 34 relevant studies [6]. Overall behavioural interventions appeared to be effective, however, it appeared that intervention content, not intensity, was related to effectiveness. There were four important features of effective weight maintenance interventions, all of which are consistent with self-regulation theory [7]; these being goal setting, self-monitoring of weight and behaviour, action plans for weight control through dietary and physical activity behaviours, and plans to deal with risk factors for weight regain and relapse prevention. The review authors also noted that thus far most weight maintenance interventions have been resource intensive and consequently not likely to be scalable. Additionally, information on the cost effectiveness of interventions was very sparse.

### Self-weighing

Given that weight regain after successful weight loss is the norm, we need cost effective weight maintenance interventions. One promising behavioural strategy is regular self-weighing to check progress against a target, a form of self-monitoring. The potential efficacy of self-weighing has been based on the principles of self-regulation theory [7] and the relapse prevention model [8]. There are three distinct stages; self-monitoring, self-evaluation and self-reinforcement [7]. Self-monitoring means systematic self-observation, periodic measurement and recording of target behaviours to increase self-awareness. The awareness promotes and sustains behaviour change through self-evaluation. Self-weighing can provide feedback of how diet and exercise behaviours affect weight and also provide negative or positive self-reinforcement of relevant behaviours. Regular self-weighing may also act as a primer, increasing self-awareness of environmental cues to eat and be inactive [9]. Self-weighing is less cumbersome than monitoring diet and physical activity and may allow people to detect changes in their weight earlier, take immediate action and see the consequences on their weight. It may aid self-management of weight in a manner that could be sustained in the longer term and so have a public health benefit [10].

### Previous research

There have been trials of weight management that have included self-weighing as part a multicomponent programme and these have shown that participants can adhere to daily self-weighing and are effective [5, 11, 12]. However only one trial has included self-weighing as part of a multicomponent intervention to promote weight loss maintenance and the intervention group regained significantly less than the control group at 18 months follow-up [5]. The intervention showed promise, however it would be costly to deliver as it involved face to face sessions and therefore unlikely to be implemented as part of a weight management service within most health systems.

### Pilot work

Previously we have evaluated an intervention to facilitate weight maintenance and prevent weight regain over the longer term in users of a weight management service called Lighten Up [13]. Users of the Lighten Up service were offered a three month weight maintenance intervention after completing their weight loss programme and nine month follow-up data were collected. The intervention focused on encouraging regular self-weighing. Participants who did not own scales were given a voucher to obtain a free set from a local pharmacy and sent a chart to record their weight on a weekly basis and a hints and tips booklet about strategies to facilitate weight management. Participants were telephoned three months later to encourage regular adherence to weekly weighing. The intervention was delivered by call centre staff with no specialist behavioural skills and minimal training. We examined the efficacy of this self-weighing focused weight maintenance intervention on weight regain at nine months by comparing the weight of those offered the intervention (intervention group) (n = 3,290) with participants (n = 478) in the preceding Lighten Up trial [13] who had not received a maintenance intervention (control group). Using intention to treat analysis, both groups regained weight but the intervention group regained 0.7 kg (95 % CI 0.1 to 1.2) less than the control group. In the per protocol analysis, comparing intervention participants who had accepted the maintenance intervention with controls, the mean difference was much larger at 3.0 kg (95 % CI -3.7 to -2.3). Whilst our pilot results were encouraging and offer preliminary evidence to support the intervention, participants were not randomised to the groups, the intervention was not optimally configured to encourage behaviour change, follow-up data were mostly self-reported and the frequency of self-weighing was not recorded.

The effectiveness of the intervention therefore needs to be established with a more robust study. Therefore the primary aim of this study is to evaluate the effectiveness and cost effectiveness of a brief behavioural intervention delivered by non-specialist staff to promote regular self-weighing to prevent weight regain after intentional weight loss. The intervention will be compared with the comparator group. The research will test a theoretically informed weight loss maintenance intervention, following successful completion of standard widely available commercial and National Health Service (NHS) weight loss programmes.

## Methods/Design

### Ethical approval

Ethical approval (ERN_13-138) was reviewed and obtained by the Science, Technology, Engineering and Mathematical review committee at the University of Birmingham, UK. The committee reviewed and approved all study materials on the 29^th^ April 2014 and will approve all study protocol amendments.

### Design

This study was designed in response to a funding call from the National Institute of Health Research Public Health Research Programme in England to answer the research question: “What behaviour change interventions are effective and cost effective in reducing the chance of relapse and sustaining healthy behaviours in smoking, alcohol use, diet or physical activity.” The design is an RCT of 560 adults who will have received a publically funded weight loss programme for 12 weeks and lost at least 5 % of their initial body weight.

### Setting and recruitment

All participants in a Public Health funded weight management service will be sent an invitation letter from their service on behalf of the research team, as well as an information leaflet, when they reach week nine of their weight loss programme. The letter will inform participants about this weight loss maintenance study (called LIMIT) and will notify them that as part of the routine service they will be asked whether they are willing to take part in a study to prevent them regaining the weight they may have recently lost. At week 11 of the weight loss programme participants will be asked to report their current weight to enable the research team to calculate the total amount of weight loss since starting their weight loss programme. Those who have lost at least 5 % of their starting weight will be asked by members of the research team to participate in a study about preventing weight regain. Figure 1 depicts participant flow through the trial.

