### Exclusion criteria

Women who are known to be pregnant or intending to become pregnant during the study.

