*Barrier identification/ Problem solving*	The telephonists offer practical solutions and give participants ideas and strategies to overcome barriers to daily self-weighing. Participants will be advised that if their current weight is more than 1 kg above target weight then they would be best to restart following the plan they followed for eating and physical activity when they were on their weight loss programme.
*Agree behavioural contract*	The telephonist asks participants if they can commit to a weight change target and to daily weighing.
*Provided general encouragement*	The telephonist encourages the participant ‘*remember every time you record your weight you are one step nearer to this becoming a healthy habit’*’
*Prompt self-monitoring of behavioural outcome*	Participants will be advised to weigh themselves daily and record it on the record card provided
*Prompt social support*	Prompt participants to ask someone they care about to support them. Participant are advised to tell this person their goal and ask them to remind the participant of this goal and check commitment to it and whether it has been achieved every week.

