### Assessments

#### Baseline

A researcher measures participant’s height and weight at a home visit before randomisation. Participants complete the baseline questionnaire and answer the open ended questions about their previous weight loss attempts and strategies they use to control their weight before being randomised. As a process measure the intervention group will be given a set of BodyTrace scales to use to weigh themselves, these scales transmit weight data to a remote database to provide an objective measure of weighing frequency (see below).

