### Process measures

We are collecting process measures to monitor recruitment, intervention delivery and potential variables that may mediate the outcomes. Our hypothesis is that self-weighing leads to the development of conscious cognitive restraint, which the National Weight Control Registry has found to be a key behavioural attribute associated with weight maintenance [17]. Using six items from the revised three factor eating questionnaire [16] we will examine if feedback from self weighing has led to development of conscious cognitive restraint of eating (measured in both groups) at three, six and 12 months post randomisation. In the intervention group we will use seven items from the index of habit strength [18] to measure the automaticity of self-weighing and five items from Steinberg [12] to measure perceptions of daily self weighing at the same follow-ups. At three, six and 12 months follow up participants in both groups will be asked to complete a series of open ended questions about any weight control practices they may have used in the previous two weeks, which will be coded. Within these questions we will specifically ask participants whether they have reapplied any behavioural techniques they acquired through participation in their weight loss programme and whether they have re-enrolled in a weight loss programme. We will then be able to examine whether the intervention may work by encouraging people to reapply lessons and techniques they learnt on the weight loss programme or it works by encouraging participants to enrol in a weight loss programme once more. Table 2 documents the process measures collected.

**Table 2 Tab2:** Measurements and study questionnaires at baseline and follow-ups

Reach		
Number of participants eligible		
Number of participants consented		
Number of participants consented and randomised		
Intervention		
	Comparator group	Intervention group
Frequency of recording self-weighing –record cards		X^a^
Frequency of self-weighing (objective scales)		X
Psychological Measures		
Index of habit strength [18]		X
Energy restriction [16]	X	X
Perceptions of self-weighing [20]		X
Thoughts about regular weighing (open ended questions)		X
Weight locus of control [21]	X	X
Weight loss strategies		
Weight control strategies (including frequency of self-weighing) [22]	X	X
Attendance at commercial weight loss programmes & application of skills learnt at weight loss programme (open ended)	X	X

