### Randomisation

The randomisation list will be developed by an independent statistician within the Primary Care Clinical Research and Trials Unit using NQuery Advisor. Participants will be randomised to the intervention or comparator groups on a 1:1 basis using random permuted blocks of varying size. Some people who have lost weight will want to continue attending the weight management group and pay themselves, after completing the NHS-provided 12 week course, and this is likely to have an important effect on weight at 12 months. To ensure this effect is balanced by treatment arm we will stratify randomisation by whether participants intend to continue with their weight loss programme or not.

Participants will be randomised at the baseline appointment after consent is gained and eligibility checked. The research assistants will be operating in participants’ homes and out of office hours so the only option available will be to implement randomisation by opaque sealed envelopes. These will be sequentially numbered and research assistants open these in sequence and the trial manager checks their adherence to this instruction regularly.

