### Blinding

In the information sheet participants will not be told that this is a trial about target setting and daily weighing and will therefore be blinded to group allocation. Instead they will be told that it is a trial of different strategies to prevent weight regain after weight loss. After randomisation the intervention group will know they have been allocated to the weighing group as they will receive a set of weighing scales but the comparator group will remain blinded that the intervention group are being asked to weigh themselves daily. We will also ensure researchers taking follow-up outcome measures will be blinded to group allocation by providing the trial documents in a sealed envelope with a sticker on the front to record the weight of the participant prior to asking questions specific to their trial arm, which inevitably would reveal the random allocation. The researcher undertaking weight measurements (primary outcome) will not have collected baseline or three month measurements therefore remain blind to group allocation. Participants will be asked not to reveal their group allocation to researchers at follow-up. The trial statistician will remain blinded to group allocation until analysis is completed.

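### Nothing stops two members of one household being randomised to opposite arms, where the stated blinding of the comparator to daily weighing is unlikely to hold; the likely effect is small

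*Protocol article*

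**What the plan says.** Setting and recruitment casts the net over the whole service: "All participants in a Public Health funded weight management service will be sent an invitation letter from their service on behalf of the research team". The inclusion list covers age, a phone that can receive texts, sufficient English and the qualifying weight loss. The exclusion list has one entry: "Women who are known to be pregnant or intending to become pregnant during the study". Neither list mentions household.

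Under Randomisation, allocation is by individual: "Participants will be randomised to the intervention or comparator groups on a 1:1 basis using random permuted blocks of varying size". It is carried out in the participant's home with sequentially numbered sealed envelopes. The only stratifier is programme intention: "we will stratify randomisation by whether participants intend to continue with their weight loss programme or not". Nothing provides for allocating members of one household together.

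The Blinding section says that, after randomisation, "the comparator group will remain blinded that the intervention group are being asked to weigh themselves daily". The safeguards it describes are a neutral information sheet, outcome assessors who do not know the allocation, and a request that participants not reveal their arm to researchers. None of these concerns what one participant learns from another.

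The intervention is visible at home. According to the Baseline section, "the intervention group will be given a set of BodyTrace scales to use to weigh themselves". Table 1, under Intervention components, suggests keeping the scales in the bathroom as a cue, and includes this technique: "Prompt participants to ask someone they care about to support them". That supporter is to be told the goal and asked to check on it weekly.

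**The concern.** Eligibility and allocation, as written, are at odds with the blinding statement in one identifiable situation. If two people in one home both qualify, staff who follow the printed criteria would enrol both and open the next envelope for each. When the envelopes differ, the comparator member lives alongside the scales, the record card and the reminder texts, and could even be the chosen supporter. That person is then unlikely to stay unaware that the other arm weighs daily, and may take up the practice.

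What is at stake is the contrast between the arms. A comparator who adopts daily weighing moves towards the intervention arm, so the estimated difference in weight change at 12 months is pulled towards zero. This arises from the eligibility and allocation rules themselves, so an analysis plan written later cannot prevent it.

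**Working it through.** **Inputs from the Sample size section.** Difference d = 2 kg; standard deviation (SD) of weight change 6.3 kg; 90 % power; 5 % significance (two-sided assumed, since a one-sided test would need only 170 per arm before dropout and does not match); 25 % loss; 280 per arm, 560 in total.

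**Reproducing the plan's figure.** n per arm = 2 × (1.960 + 1.282)² × 6.3² / 2² = 209 after rounding up. Allowing for loss, 209 / 0.75 = 279 per arm, or 558 in total, against 560 stated. With 280 × 0.75 = 210 completers per arm, the standard error is 6.3 × √(2/210) = 0.615 kg, and power = Φ(2/0.615 − 1.960) = 90.2 %. The sample size is correct as stated.

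**Assumptions, because the article gives no figure.** A share h of the 560 participants enter as two-person household pairs. The two members are allocated independently, so half of the pairs are split. Every comparator in a split home gains the whole 2 kg effect, which is the extreme case for uptake.

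**From h to the exposed share.** Pairs = h × 560 / 2 = 280h. Split pairs = 140h. Each split pair contains one comparator, so the exposed share of the comparator arm is 140h / 280 = h/2.

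**Diluted difference and power.** d' = 2 × (1 − h/2); power = Φ(d'/0.615 − 1.960).

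| Share in pairs, h | Pairs | Split homes | Comparators exposed | Difference | Power |
|---|---|---|---|---|---|
| 0 | 0 | 0 | 0 % | 2.00 kg | 90.2 % |
| 2 % | 5.6 | 2.8 | 1 % | 1.98 kg | 89.6 % |
| 5 % | 14 | 7 | 2.5 % | 1.95 kg | 88.7 % |
| 10 % | 28 | 14 | 5 % | 1.90 kg | 87.1 % |
| 20 % | 56 | 28 | 10 % | 1.80 kg | 83.3 % |

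Power falls below 80 % only when about 14 % of comparators are fully exposed, that is, with about 2 × 14 = 28 % of participants in pairs. If exposed comparators gained half the effect, the 10 % row would become 2 × (1 − 0.05 × 0.5) = 1.95 kg.

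**A limit of the calculation.** Two people who take consecutive envelopes from the same permuted block are split somewhat more often than half the time. The article gives no block sizes, so I keep one half as the working value.

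**The case against.** The strongest objection is that this is silence in a condensed article, that the share of paired participants is assumed, and that even the extreme case costs at most 0.1 kg over the 2-10 % range. Comparators receive no calls, target, record card or texts of their own, so full uptake is implausible. The blinding statement describes an arm, and a few split homes do not undo it for the arm. The article does not say that couples attend together, or that the supporter lives in the home.

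Most of this stands, and it fixes the size of the point. It does not remove it. The article prints both eligibility lists and the allocation method, and staff following them would enrol and separate such pairs. The blinding statement has no qualification for that case.

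A reader might go further in three directions that the document does not support.

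- **The same person randomised twice.** The Process measures section does ask participants "whether they have re-enrolled in a weight loss programme". A second randomisation would need re-entry to the publicly funded service, a second qualifying loss, and a second consent with the same team. Nothing in the text suggests this. Table 2 refers to commercial programmes, and the Randomisation section expects people who continue to pay for themselves.
- **Invalid analysis through non-independence.** With individual allocation, positive correlation within a home lowers the variance of the between-arm difference for split pairs and raises it for same-arm pairs. The two roughly offset, and no material error is shown.
- **Corrupted scale data.** Any cohabitant could step on the scales, whether or not in the trial, so a household exclusion would not solve that. The scales also transmit the weight itself, so another adult's readings could often be recognised. They supply process data, while the primary outcome is weight taken by researchers.

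**Conclusion.** The point holds in limited form. The printed eligibility criteria and individual randomisation allow members of one household to be placed in opposite arms, and in those homes the blinding statement is unlikely to be true. The bias is towards no difference and is confined to split homes.

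Its size rests on three assumptions: 2-10 % of participants in pairs, half of the pairs split, and full uptake by every exposed comparator. On these, the expected difference falls from 2.00 kg to between 1.98 and 1.90 kg, and power from 90.2 % to between 89.6 % and 87.1 %. Partial uptake gives less. The trial's validity and its sample size are not in question. This is a minor improvement, worth making because it is cheap.

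**What to change.** Add to Exclusion criteria: *lives in the same household as a participant already randomised in LIMIT*. Ask about it at the week 11 contact and check the answer against the trial list. Two cohabitants on the same programme may reach week 11 before either is randomised, so confirm it again at the home visit before the envelope is opened.

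The cost is one question and a list check at contacts that already take place, plus the loss of a few otherwise eligible people. If the sponsor prefers not to exclude them, the minimum is to qualify the blinding statement and record which participants share a home.
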